## Interventions

### Explanation for the choice of comparators {6b}

Photogrammetry will be evaluated with 3D scanning and conventional impression method for craniomaxillofacial defects using a software analysis.

### Intervention description {11a}

#### Introduction

Facial mutilation and deformities can be caused by cancer, tumours, injuries, infections, and inherited or acquired deformities and has the potential to degrade one’s quality of life by interfering with fundamental tasks like communication, breathing, feeding, and aesthetics.

Depending on the type of defect, producing maxillofacial prostheses for the rehabilitation of patients with various defects can be challenging and complex. The prosthesis is used to replace missing or damaged parts of the cranium and face, like the nose, auricle, orbit, and surrounding tissues, as well as missing areas of soft and hard tissue, with the primary goal of increasing the patient's quality of life by rehabilitating oral functions such as speech, swallowing, and mastication [3].

Traditional maxillofacial prosthesis impression and fabrication processes include a number of complicated steps that are costly, time-consuming, and uncomfortable for the patient. These rely on the knowledge of the maxillofacial team, dental clinicians, and maxillofacial technician [1].

The foundation of the impression is the keystone for creating a prosthesis. However, this is the most time-consuming and difficult chair-side operation in maxillofacial prosthesis manufacturing since it requires prolonged interaction with the patient. The field of prosthesis fabrication is being transformed by the digital revolution. Digital technology allows for more accurate impression data to be gathered in less time (3 to 5 min) than traditional methods, lowering patient anxiety. Digital impressions eliminate the need for messy impression materials and provide patients with a more pleasant experience [1]. This method by pass the procedure of traditional gypsum model fabrication. This eliminates the disparity caused by a dimensional distortion of the impression material and gypsum setting expansion. Traditional dental impression processes leave enough room for errors, such as voids or flaws, air bubbles, or deformities. While current technology for prosthesis planning has emerged as an alternative means to improve patient acceptability and pleasure, not only because the end result is a precisely fitted restoration but also because the chair-side adjustments required are reduced [2].

The most frequent approaches for creating 3D virtual models are the following. To begin, 3D scanning is employed, in which the subjects are scanned in three dimensions, and the point cloud data is used to create a virtual digital model.

Photogrammetry is the second method, which uses finite pictures taken from various perspectives to create 3D digital models. When compared to traditional data collection methods, the two methods are non-contact and save time. Though 3D scanning is a quick and accurate process, it has drawbacks such as a high set-up cost and the need for expert labour. Because of these drawbacks, this technology is only used in prosthetic design on a very limited basis. With a little compromise in 3D modelling accuracy, the photogrammetry method can overcome the drawbacks of 3D scanning. It primarily offers advantages such as the usage of freeware for model creation, the ability to handle the method with semi-skilled people, and the ability to produce good results even with a phone camera using standard operating procedures [4].

The initial step in the photogrammetry approach is to collect photos from all angles; after that, post-processing can be done by a professional using photogrammetry software and CAD/CAM tools. The photogrammetrically formed 3D model can then be used to create a mould, which can be compared against moulds fabricated via 3D scanning and traditional methods [5].

Because the prosthodontist may review the digitally scanned impression at the chairside just by magnifying it, any problems can be corrected before the data is sent to the dental laboratory [6]. However, the complete manufacture of the prosthesis using rapid prototyping is expensive, and the final prosthesis creation is fully dependent on the donor anatomy [7].

When compared to a manually modelled prosthesis, a 3D-produced prosthesis made from the mirror image of the undamaged portion or from the donor does not provide improved aesthetics. The art of sculpturing and adding uniqueness into the prosthesis can be added using the traditional wax-up procedure [8]. Other laboratory procedures can be done using the traditional way to keep costs down and make the prosthesis more appealing [9–11]. 

The purpose of this research is to assess and compare conventional impression techniques, photogrammetry, and 3D scanning methods of impression making and casting by rapid prototyping for the manufacturing of maxillofacial prostheses with better precision and fit while reducing chair side time and minimising patient contact while keeping costs low.

### Criteria for discontinuing or modifying allocated interventions {11b}

There will be no special criteria for discontinuing or modifying allocated interventions

### Strategies to improve adherence to interventions {11c}

Not applicable as there are no follow-ups involved in the study. The outcomes will be checked on the day of prosthesis insertion therefore adherence to intervention will not be an issue because the patients will be evaluated for primary and secondary outcomes on the day of prosthesis insertion because cranioplasty is an elective surgical procedure carried out for the purpose of improving aesthetics and in some cases function. We are using PMMA flaps for cranioplasty procedures which have a complication rate of 9.2–23% (most commonly infection) according to a study by Enrique-Caro-Osiro et al. Further studies have shown a slight decrease in infection rate when performed within 3 months of craniectomy (Fig. 1).

**Fig. 1 Fig1:**
[figure not shown]
Study period

### Relevant concomitant care permitted or prohibited during the trial {11d}

Not applicable because there is no concomitant care permitted or prohibited during the trial because cranioplasty is elective surgical procedure carried out for the purpose of improving aesthetics and in some cases function. We are using PMMA flaps for cranioplasty procedures which have a complication rate of 9.2–23% (most commonly infection) according to a study by Enrique-Caro-Osiro et al. Further studies have shown a slight decrease in infection rate when performed within 3 months of craniectomy.

### Provisions for post-trial care {30}

Not applicable as there is no follow-up involved in the study as cranioplasty is an elective surgical procedure carried out for the purpose of improving aesthetics and, in some cases, function. We are using PMMA flaps for cranioplasty procedures which have a complication rate of 9.2–23% (most commonly infection) according to a study by Enrique-Caro-Osiro et al. Further studies have shown a slight decrease in infection rate when performed within 3 months of craniectomy.

### Outcomes {12}

The study would help in predicting the best method for craniomaxillofacial impression procedures.

The final prosthesis will be evaluated for precision, fit, accuracy, functional affectivity, time involved in comparison with conventional, photogrammetry and 3D scanning technology. The low-cost setup of the photogrammetric method gives the advantage of minimum chair side time and less patient exposure which is very much advantageous in the COVID era.

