**Methodology:**

1. Patient screening will be done, and the patient will be allocated to three techniques that are the conventional manual method, photogrammetry method, and 3D scanning in a randomised manner

2. The impression of the defect will be recorded by conventional manual method, photogrammetry method, and 3D scanning

3. The defect will be modelled in three ways: first is as per the manual dimension taken on the patient, second is the organisation of photographic image taken with lab standards and third is plotting of point cloud data to generate the virtual 3D model

4. For photogrammetric prosthesis design, finite photos/images will be taken at multiple angles to model the 3D virtual design. With the use of minimum photographs, the 3D modelling can be performed by using freeware, and a mould is obtained

5. The CAD software was used to design the prosthesis, and the final negative mould can be printed using additive manufacturing

6. The mould fabricated by all three methods will be analysed by a software using reverse engineering technology

**Study design**: Randomised control trial

**Duration**: 2 years

**Sample size**: 45 patients

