## Data collection and management

### Plans for assessment and collection of outcomes {18a}

Software analysis of all the prostheses fabricated by all three ways

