### Plans to promote participant retention and complete follow-up {18b}

Not applicable as there are no follow-ups involved in the study. The outcomes will be checked on the day of prosthesis insertion; therefore, adherence to intervention will not be an issue because the patients will be evaluated for primary and secondary outcomes on the day of prosthesis insertion because cranioplasty is an elective surgical procedure carried out for the purpose of improving aesthetics and, in some cases, function. We are using PMMA flaps for cranioplasty procedures which have a complication rate of 9.2–23% (most commonly infection) according to a study by Enrique-Caro-Osiro et al. Further studies have shown a slight decrease in infection rate when performed within 3 months of craniectomy.

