## Statistical methods

### Statistical methods for primary and secondary outcomes {20a}

Analytical tests like chi-square test and Student’s *t*-test will be performed. All the statistical analysis will be performed; *p* 0.05 will be considered as the level of significance.

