### Methods for additional analyses (e.g. subgroup analyses) {20b}

#### SPIRIT guidance: methods for any additional analyses (e.g. subgroup and adjusted analyses)

As there are no subgroups in the study, the subgroup analysis will not be carried out. The population will be studied under three groups—conventional impression, 3D scanning, and photogrammetry—so there is no role of subgroups.

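### Five outcomes stand on equal footing with no primary named, and the object analysed by software is the mould in some sections and the prosthesis in another, so the deciding result can be chosen after the data are seen.

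*Protocol article*

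**What the plan says.** **Outcomes.** Outcomes {12} sets the aim, "The study would help in predicting the best method for craniomaxillofacial impression procedures", and then lists five outcomes side by side: "The final prosthesis will be evaluated for precision, fit, accuracy, functional affectivity, time involved in comparison with conventional, photogrammetry and 3D scanning technology". None is called primary.

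**Primary and secondary.** Item {18b} says that "the patients will be evaluated for primary and secondary outcomes on the day of prosthesis insertion". Items {11c} and {21b} say the same, and the heading of {20a} uses the same split. No section says which outcome is which. Among the Objectives {7}, only the fourth names an outcome: accuracy of the impression procedures, evaluated with software. It is not called primary.

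**Object measured.** The Abstract's methodology list, Study setting {9} and item {33} say: "The mould fabricated by all three methods will be analysed by a software using reverse engineering technology". Item {18a} instead plans "Software analysis of all the prostheses fabricated by all three ways", and {12} evaluates the final prosthesis.

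**Tests.** Item {20a} names the chi-square test and Student's t-test and says that "0.05 will be considered as the level of significance", with no adjustment. Sample size {14} lists chi-square, one-way ANOVA and the Tukey multiple comparison test. Item {20b} confirms the number of arms: "The population will be studied under three groups—conventional impression, 3D scanning, and photogrammetry".

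**The concern.** A trial that sets out to identify the best of three methods has to say in advance which measurement decides. Here two choices stay open: which of five outcomes counts, and whether the software comparison is made on the mould or on the prosthesis. If the methods rank differently on fit, accuracy and time, or on mould and prosthesis, any of those rankings could be reported as the main result and still agree with some part of the protocol. The error rate of that main result would then be unknown.

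The conflict over tests adds to this. With three arms, whether the pairwise comparisons within an outcome are adjusted changes the false-positive rate materially, and the two sections give different answers.

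**Working it through.** **1. Does the sample size reveal an implied primary outcome?** Sample size {14} uses the single-proportion precision formula n = z²·P·(1−P)/d², with z = 1.96, P = 0.03 (prevalence of craniomaxillofacial defects) and d = 0.05:

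n = 1.96² × 0.03 × 0.97 / 0.05² = 44.72, rounded up to 45.

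This reproduces the protocol's 45 (it prints 44.71). The inputs are a prevalence and a margin of error. None of the five outcomes and no comparison between methods enters, so the calculation does not point to a primary outcome.

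**2. Number of comparisons.** Three groups give 3 pairs per outcome, and 5 outcomes × 3 pairs = 15 pairwise comparisons.

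**3. Chance of at least one false pairwise difference when the methods do not differ.** The protocol gives neither an allocation ratio nor correlations between outcomes. Assumptions: 45/3 = 15 per group; five continuous, normal outcomes with one variable each; one measured object; outcome correlation of 0, 0.5 or 0.8.

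*Under {20a} (unadjusted t-tests at 0.05).* Treating all 15 tests as independent would give 1 − 0.95¹⁵ = 53.7%. That is too high, because pairs within an outcome share arms. By simulation, three unadjusted t-tests on one outcome have a familywise error of about 12.2%. Five independent outcomes then give 1 − (1 − 0.122)⁵ = 48%.

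*Under {14} (Tukey within each outcome).* The three pairs are held at about 5% per outcome. Five independent outcomes give 1 − 0.95⁵ = 22.6%.

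Simulated results:

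| Outcome correlation | {20a}: unadjusted t-tests | {14}: Tukey per outcome |
|---|---|---|
| 0 | 48% | 23% |
| 0.5 | 40% | 19% |
| 0.8 | 29% | 13% |

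**4. Chance of a false best method.** The protocol has no rule for declaring one. Suppose it means a method significantly better than both others on at least one outcome. The same simulation then gives 6.7%, 6.0% and 4.4% for unadjusted t-tests, and 2.0%, 1.9% and 1.5% with Tukey, at correlations 0, 0.5 and 0.8. A looser rule would give more.

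**5. After the fix.** With one primary outcome and Tukey across its three pairs, the familywise error is about 5% (simulated 4.9% to 5.0%).

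**The case against.** **Tukey is already named.** Item {14} lists it, so 15 unadjusted comparisons follow only from {20a}. This stands. On the {14} reading there are five families, each controlled at about 5%, and the figures roughly halve. What remains is that the two sections disagree.

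**Adjustment across outcomes can wait for the analysis plan.** This also stands, so the absence of a cross-outcome adjustment is not the complaint. The primary outcome is a different matter. It belongs in the Outcomes section, which is present, and other sections depend on it.

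**Accuracy is the implied primary outcome.** Objective 4 favours it, but no section says so, and {12} gives it no precedence.

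**A false best method is likely.** A reader might infer this from the 48%. The documents do not support it: one false difference between two of three methods does not make a method best, and under the strict rule above the chance is 7% or less.

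**Measuring the prosthesis dilutes true differences, so only the mould is right.** A reader might infer this because the Intervention description {11a} mentions traditional wax-up and laboratory steps. It offers them as options in a background account, and the methodology in {9} does not list wax-up. The purpose stated in {11a} also includes the precision and fit of the prosthesis, so the prosthesis is a defensible object as well.

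**The plan prejudges photogrammetry.** Item {12} says "The low-cost setup of the photogrammetric method gives the advantage of minimum chair side time and less patient exposure". That is advocacy placed among the outcomes, but it changes no analysis and is not part of this point.

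**Conclusion.** The concern holds in a limited form. The protocol relies on a primary outcome that it never names, and it contradicts itself on the object analysed by software. Both are plain from the text and need no calculation. Together they leave the deciding result open to choice after the data are seen.

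The multiplicity figures show what that openness could cost: a 29% to 48% chance of some false pairwise difference if {20a} is followed, and 13% to 23% if {14} is followed, against a nominal 5%. They rest on 15 patients per group, five continuous outcomes with one variable each, and assumed correlations of 0 to 0.8. Both test lists include chi-square, so some outcomes may be categorical and the figures would then shift. They do not measure the risk of wrongly naming a best method, because the protocol states no rule for doing so.

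**What to change.** 1. In {12}, name software-measured accuracy, the outcome of objective 4, as the single primary outcome.
2. State one measured object in {9}, {12}, {18a} and {33}, and align the Abstract with it. The mould is closest to the impression-accuracy objective, but the documents do not settle the choice, and the passages must be reconciled.
3. Make {20a} agree with {14}: one-way ANOVA with Tukey for the three pairwise comparisons on the primary outcome.
4. Base any statement about the best method on the primary outcome, and label the other four outcomes secondary and exploratory.

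**Cost.** No extra patients or measurements are needed to name the primary outcome. Trial status says that recruitment began in September 2022, so this is a protocol and registry amendment during recruitment, and it should be made before anyone examines outcome data. The price is that precision, fit, functional effectiveness and time can no longer support a confirmatory claim.

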### Participant timeline {13}

The participant timeline is as follows: 25 October 2022 to 25 August 2023.

### Sample size {14}

45 Daniel formula for sample size calculation$$n=\frac{Za/{2}^2\cdot P\cdot \left(1-P\right)}{d^2}$$where*Zα*/2^2^ is the level of significanceAt 5%, i.e. 95% confidence interval = 1.96*P* = prevalence of craniomaxillofacial defects = 3% = 0.03*d* = desired error of margin = 5% = 0.05$$n=\frac{1.96^2\times 0.03\times \left(1-0.03\right)}{0.05^2}=44.71$$*n* = 45 patients needed for the study

Study reference: Mohamed Khallaf et al.

Formula reference: Daniel et al.

Statistical method: chi-square test, one-way ANOVA, Tukey multiple comparison test

Software used: SPSS 27.0 V and Graph Pad Prism 7.0V

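### The 45 patients come from a formula for estimating a prevalence, so their power for the three-method accuracy comparison is unknown

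*Protocol article*

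**What the plan says.** Sample size {14} gives a full derivation. The formula is n = z² × P(1 − P)/d². The confidence input is "95% confidence interval = 1.96", the proportion is "prevalence of craniomaxillofacial defects = 3% = 0.03", and the precision is "desired error of margin = 5% = 0.05". The result is 44.71, and the section concludes "45 patients needed for the study".

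The same section then lists the analysis: "Statistical method: chi-square test, one-way ANOVA, Tukey multiple comparison test". Statistical methods {20a} lists a different set: "Analytical tests like chi-square test and Student’s" *t*-test.

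The comparative aim in Objectives {7} is the accuracy of conventional, photogrammetric and 3D-scanned impressions. The additional-analyses section {20b} describes separate groups: "The population will be studied under three groups—conventional impression, 3D scanning, and photogrammetry". Outcomes {12} lists what is measured: "The final prosthesis will be evaluated for precision, fit, accuracy, functional affectivity, time involved". None of these sections gives an SD, a difference of interest or a target power.

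**The concern.** The formula sizes a survey that estimates one proportion to within a chosen margin. Here the proportion is how common craniomaxillofacial defects are. This trial does not estimate that. Eligibility {10} admits only people with an extraoral defect, and recruitment is from a prosthodontic outpatient clinic, so the prevalence in the sample is 100% by design. The margin of 5 points is likewise not a difference between methods.

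The quantities that decide whether a three-method comparison is informative are absent: the size of difference that matters, the variability of the accuracy measure, the power, the number of groups and the allocation ratio. The formula would return 45 for two methods or for ten.

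At stake is how the result is read. The article says that 45 patients are what the study requires, and a reader would assume that this number was set for the comparison. It was not, so nothing in the text tells the reader which differences in accuracy the trial could detect or rule out.

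**Working it through.** **1. The plan's own figure.** Inputs from Sample size {14}: z = 1.96, P = 0.03, d = 0.05.

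n = 1.96² × 0.03 × 0.97 / 0.05² = 44.716, rounded up to 45. The stated figure reproduces. The fault is the choice of formula, not the calculation.

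**2. What the formula delivers.** At n = 45 and P = 0.03 the half-width is 1.96 × √(0.03 × 0.97/45) = 0.0498, so the interval is about −2.0% to 8.0%, with 45 × 0.03 = 1.35 expected cases. The margin exceeds the proportion being estimated. This is secondary, because the trial has no use for that interval.

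**3. What 45 delivers if the groups are parallel.** Assumptions not in the document: 15 per group, a continuous and roughly normal accuracy measure, two-sided 5%. Differences are in units of the outcome SD.

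- One-way ANOVA (noncentral F, 2 and 42 df): power is 8% at f = 0.10, 28% at 0.25, 64% at 0.40 and 83% at 0.50. It reaches 80% at f = 0.48. With the third mean midway between the extremes, f = 0.48 means extremes 0.480 × √6 = 1.18 SD apart. With two methods equal and one different, it means 0.480 × 3/√2 = 1.02 SD.
- One pair, Tukey: the critical value is the studentized range 3.436/√2 = 2.429 on 42 df. Power is 80% at about 1.20 SD and 16% at 0.5 SD.
- One pair, unadjusted two-sample *t*-test: power is 80% at 1.06 SD and 26% at 0.5 SD.
- 95% CI half-width for a pairwise difference, unadjusted: 2.018 × √(2/15) = 0.74 SD. As a Tukey simultaneous interval: 2.429 × √(2/15) = 0.89 SD.

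**4. What 45 delivers if every patient receives all three methods.** The SD of a within-patient difference is SD × √(2(1 − ρ)), where ρ is the correlation between methods in one patient (assumed). A paired *t*-test with n = 45 has 80% power at 0.427 SDs of the difference (two-sided 5%), or 0.499 with Bonferroni for three pairs (5%/3). Multiplying by √(2(1 − ρ)):

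| ρ | Unadjusted | Bonferroni |
|---|---|---|
| 0 | 0.60 SD | 0.71 SD |
| 0.5 | 0.43 SD | 0.50 SD |
| 0.8 | 0.27 SD | 0.32 SD |

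**5. Which design applies.** Section {20b} points to three separate groups. The methodology list (Abstract, and Study setting {9}) first allocates patients at random to the techniques, but its next steps can be read as recording and modelling each defect in all three ways. The allocation sections {16a–c} give no ratio. The detectable pairwise difference therefore runs from about 1.2 SD (parallel, Tukey) down to 0.27 SD (within-patient, ρ = 0.8, unadjusted), and the document does not say where in that range the trial lies.

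**The case against.** **An analysis plan or fuller protocol may hold a proper power calculation.** It may, and silence on power in an article would not be a finding by itself. Here, however, the article prints the formula, every input, the result and the claim that this number is required. A separate document cannot make a prevalence formula justify a three-method comparison. The point stands.

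**Forty-five may be quite enough.** This stands. If the differences of interest are large (f of about 0.48 or more), or if each patient receives all three methods and measurements within a patient are strongly correlated, 45 could have good power.

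Two stronger readings are tempting, and the document supports neither:

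- A reader might infer that the trial is underpowered, or that it cannot exclude large differences. Without an SD, a difference of interest, an allocation ratio or a settled design, that cannot be shown.
- A reader might infer that a non-significant result will be presented as equal accuracy. No section claims equivalence or non-inferiority. Outcomes {12} speaks of finding the best method, and the intervention description {11a} expects photogrammetry to give up a little accuracy. Reporting confidence intervals is a sensible safeguard here, not the correction of a stated error.

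**Conclusion.** The stated basis for the sample size is wrong for the trial's comparative objective, and no other section repairs it. The supported conclusion is that the power of 45 patients for comparing the three methods is unknown.

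The error in formula rests only on what Sample size {14}, Objectives {7} and Eligibility {10} say. The detectable differences are illustrations: they depend on equal groups of 15 or full within-patient data, a continuous outcome, two-sided 5% testing and, for the paired case, an assumed correlation. The point should be fixed before results are reported, because this calculation is the only justification offered for the trial's size.

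**What to change.** 1. Reconcile the design: parallel groups as in {20b}, or all three methods in each patient as the methodology list in the Abstract and {9} allows.
2. Reconcile the test: ANOVA with Tukey in {14}, or Student's *t*-test in {20a}. Use a paired or repeated-measures analysis if the design is within-patient.
3. Keep 45, and delete the prevalence formula and the statement that this number is needed. Replace them with what 45 delivers for the accuracy endpoint:
   - *If parallel:* with 15 per group, 80% power at f = 0.48, and for one pair at about 1.2 SD after Tukey adjustment (1.06 SD unadjusted). Pairwise 95% CI half-width 0.74 SD unadjusted, or 0.89 SD as a Tukey simultaneous interval. Label which one is quoted, so that adjusted power does not stand beside unadjusted precision.
   - *If within-patient:* the row of the table above for a justified correlation, unadjusted or Bonferroni as the analysis requires.
4. Convert these figures to millimetres with an SD whose source is given, and report all pairwise differences with their confidence intervals.

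The cost is protocol wording, with no extra patients and no change to procedures. The downside is a less favourable justification: it says what 45 patients can show, not that 45 is enough. That further claim would require a stated difference that matters clinically.

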### Eligibility criteria {10}

Defect size not bigger than 9 × 12 cm (3.5 × 4.5 inches)In the age group of 10–70 yearsExtra oral defects

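### The tests named for the accuracy comparison are all unadjusted; prespecifying baseline defect size as a covariate would probably improve precision at the fixed 45 patients

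*Protocol article*

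**What the plan says.** All references are to the protocol article.

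- **Aim.** Objectives {7} sets out a comparison of accuracy between conventional impression, photogrammetry and extraoral 3D scanning.
- **Eligibility {10}.** Entry is limited by size: "Defect size not bigger than 9 × 12 cm (3.5 × 4.5 inches" is the bound, and no lower limit is given. The section does not say that the dimensions are kept as data.
- **Sample size {14}.** The total is "45 patients needed for the study", followed by "Statistical method: chi-square test, one-way ANOVA, Tukey multiple comparison test".
- **Statistical methods {20a}.** "Analytical tests like chi-square test and Student’s" *t*-test are named, with a 5% significance level.
- **Additional analyses {20b}.** Subgroup analysis is ruled out, and the population is described as three groups. Adjusted analysis is not discussed, although the heading covers it.
- **Non-adherence and missing data {20c}.** Standardised effect sizes for baseline imbalance are to feed into multivariable modelling. No covariate or outcome is named. The same section speaks of shared decision-making and a decision aid, which are not part of this trial.

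**The concern.** Every test that the protocol names for a continuous outcome compares raw group means. If each patient receives one technique, any variation in accuracy that comes from defect size goes into the error term. The permitted range is wide, from any small extraoral defect up to 9 × 12 = 108 cm². It is plausible, though not documented, that larger pieces deviate more.

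Defect size is fixed before allocation and must be assessed at screening to apply the eligibility limit, so it is a natural covariate. With 45 patients in three groups, precision is scarce and this source of it is nearly free. At stake is the width of the confidence intervals for the differences between techniques, and the power to detect them. The validity of the test is not at stake.

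Section {20c} does not supply the adjustment. Letting observed imbalance guide the model means choosing covariates after seeing the data, which is not prespecification.

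**Working it through.** **1. The plan's own figure.** Inputs from {14}: "95% confidence interval = 1.96", "prevalence of craniomaxillofacial defects = 3% = 0.03" and "desired error of margin = 5% = 0.05".

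n = 1.96² × 0.03 × 0.97 / 0.05² = 44.716, rounded up to 45. The protocol prints 44.71, so the figure reproduces. The formula concerns the precision of a prevalence estimate. It contains no power, standard deviation or effect size for accuracy, so there is no planned power against which to measure a loss.

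**2. What has to be assumed.**
- 15 patients per group (the documents give three groups but no ratio).
- One technique per patient.
- An overall F test at the 5% level stated in {20a}.
- A correlation rho between defect size and the accuracy measure within groups. The documents give no value, so a range is shown.

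**3. Formulae.** Let f be the standardised effect (the SD of the group means divided by the within-group SD).
- Unadjusted: noncentrality = 45 f², with 2 and 45 − 3 = 42 degrees of freedom.
- Adjusted for one covariate: noncentrality = 45 f² / (1 − rho²), with 2 and 45 − 3 − 1 = 41 degrees of freedom.

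Power is the probability that the noncentral F exceeds the central 95% point.

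**4. Results.** Unadjusted power is 80% at f = 0.48 (noncentrality 10.36). At f = 0.40 it is 63.5%.

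| rho | Adjusted power, f = 0.48 | Adjusted power, f = 0.40 |
|---|---|---|
| 0 | 79.9% | 63.4% |
| 0.2 | 81.6% | 65.3% |
| 0.3 | 83.7% | 67.8% |
| 0.4 | 86.7% | 71.5% |
| 0.5 | 90.4% | 76.7% |

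From 80%, the gain is therefore 1.6 points at rho 0.2, 3.7 at 0.3 and 10.4 at 0.5. It reaches 5 points at about rho 0.35. At rho 0 the loss is 0.07 point. Adjustment breaks even at about rho 0.04.

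**5. The same gain as precision and patients.** At rho 0.5 the residual variance is multiplied by 1 − 0.25 = 0.75. Confidence intervals shrink by a factor of √0.75 = 0.866, about 13%. An unadjusted trial would need 59 patients for the same power. At rho 0.3 it would need 50, and at rho 0.2 it would need 47.

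**6. Pairwise check.** A normal approximation for two groups of 15, set to 80% unadjusted power, gives 83.6% at rho 0.3 and 89.9% at rho 0.5. This agrees with the F test.

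**The case against.** The strongest reply is that nothing here is an error. One-way ANOVA with Tukey comparisons on randomised groups controls the type I error without covariates, and a statistical analysis plan often settles the choice of covariates. The first part stands. On the second, this article does fix its tests, in two sections that disagree with each other, and neither test is adjusted. The text needs rewriting in any case.

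Other objections carry weight:

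- **Adjustment is not wholly absent.** Section {20c} foresees multivariable models, and {20a} introduces its tests as examples. It would be too strong to say that the plan allows only unadjusted analysis. What can be said is that the named tests are unadjusted and that no covariate is specified.
- **The link between size and accuracy is conjecture.** No section reports it and the accuracy metric is not defined. A mean surface deviation or a percentage error might hardly vary with size.
- **The covariate may not exist as data.** Eligibility needs only a judgement that the defect is within the limit.
- **The design can be read in another way.** The methodology under {9} allocates patients to techniques, but also says the defect's impression is recorded by all three. Section {18a} likewise refers to prostheses made in all three ways. If each defect receives all three techniques, between-patient variation should be removed within patients and covariate adjustment becomes secondary.

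A reader might also infer that a chance imbalance in defect size would bias the comparison. The documents do not support that. Allocation is by computer-generated random numbers {16a}, and under randomisation chance imbalance is already covered by the test's error rate. It can mislead in a single sample, and adjustment reduces that, but it is not a systematic error.

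**Conclusion.** The point holds as a modest, low-cost gain in efficiency. The named tests leave any variation due to defect size in the residual, and {20c} does not repair this. At an effect with 80% unadjusted power, prespecified adjustment would add about 2, 4 or 10 points of power at rho 0.2, 0.3 or 0.5, against under 0.1 point lost at rho 0. These sizes rest on 15 patients per group, one technique per patient, and an assumed rho that the documents do not inform. Below about rho 0.35 the gain is under 5 points.

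The stronger statement, that the trial is definitely losing power, cannot be supported: the protocol states no power and gives no correlation. The importance is minor, and confidence that the gain is material is low.

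**What to change.** 1. Record each defect's two screening dimensions as numbers, before allocation.
2. State whether each patient receives one technique or each defect is captured by all three.
3. If one technique per patient: in {14} and {20a}, prespecify for the accuracy outcome a linear model with technique (three levels) and baseline defect size, for example the log of length × width. Report Tukey-adjusted differences of the adjusted means, and keep the unadjusted ANOVA as a sensitivity analysis. Limit this to accuracy; no case has been made for other outcomes, such as time involved.
4. If all three techniques per defect: use a within-patient (repeated-measures) analysis instead.
5. Reconcile {14}, {20a} and {20c}, so that one model is named for accuracy, the covariate is not chosen from observed imbalance, and the text about a decision aid is removed or explained.

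For the covariate model the cost is one error degree of freedom (42 to 41), two recorded dimensions and a change of wording. No patients, visits or procedures are added.
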